### Random assignment

Randomization was applied at different levels in every island included in the trial. Three different strata or geographic areas were set in Tenerife and Gran Canaria (metropolitan, northern, and southern areas). Four PHCP were randomly allocated to every stratum. Each PHCP was assigned to one of the three interventions or control arms by block permutation. La Palma and Lanzarote were geographically divided into four zones with only one PHCP available in each zone. Each of these PHCP was randomly assigned to one of the study arms. In every island, all arms were equally distributed.

Six FCUs were randomly selected from all those consenting participants at each PHCP. From all patients fulfilling inclusion criteria and consenting to participate in each PHCP, 15 were randomly selected per FCU. Exceptionally, more than six FCUs or more than 15 patients per FCU were selected, in order to recruit 90 patients at every PHCP.

While PHCP randomization was performed using block permutation at three different levels, second (FCUs) and third (patients) stage randomizations were performed by simple generation from a list of random numbers. PHCP assignment to interventions or control group was performed by the data manager.

In order to prevent potential contamination among study interventions, all FCUs at every PHCP were allocated to the same study group.

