#### Statistical methods

Generalized linear mixed models with repeated time measurements will be used to analyze changes in outcomes over time. To compare the three interventions and the control group after different follow-up periods (Baseline, 3, 6, 12, 18, and 24 months), the intervention groups will be treated as a ‘factor within.’ First, we will examine whether the intervention in Groups 1 and 2 are better than usual care, and then, we will examine whether the most intensive intervention (group 3) is better than less intensive interventions (groups 1 and 2). The purpose of these analyses is to obtain preliminary estimates regarding the incremental benefits of the intervention components [45]. For multiple comparisons, the *P* value will be adjusted with Bonferroni correction (Pc Z corrected value). In addition, the models will include a subset of covariates that are imbalanced at baseline. To identify the covariates to be included in the model, we will first fit separate models including each covariate, one at a time. The final model will include those covariates such that their inclusion changes the estimates’ treatment effect by at least 10%. As suggested in the CONSORT statement, decisions about covariates will not be based on *P* value [46,47].

To incorporate the effect of cluster analysis, a multilevel model (MLM) approach will be implemented. MLM adjusts for the clustering effects across three levels (patients, FCU, and PHCP) of the hierarchical data structure.

For the main intention-to-treat analysis comparing outcomes, all patients will be included. Standard imputation methods (i.e., mean value imputation, last observation carried forward) will be used to impute missing data depending on the pattern of missing data. All tests will be two-sided with a type I error of 5%. Statistical analyses will be performed using Statistical Package for social Sciences (SPSS v.21, Chicago, IL, USA).

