##### Sample size calculation

We estimated that 393 patients per arm (total in the study = 1,572) were needed to detect an absolute difference in Hba1c of 0.4%, assuming a common standard deviation of 1.4% [40], a two-tailed power of 90%, and an alpha of 0.05. After an additional adjustment for clustering of patients within FCU by the design effect [48], assuming 15 patients per FCU and an intra-class correlation coefficient of 0.01 (interquartile range: 0 to 0.032) based on data from the literature [49], the estimated number of patients per arm was 448 (total in the study = 1,792). Although the unit of allocation was the PHCPs, these are formed of several healthcare centers throughout the territory that only share administrative management and some services. Also, this effect was already controlled by means of the stratification. Therefore, we considered that the intra-class correlation within PHCP was insignificant, and we used instead the intra-class correlation for FCU, that is, among patients served by the same FCU. Although small, we consider that this correlation is significant.

However, sample size was increased by an additional 30% to accommodate for expected losses to follow-up and to warrant the presence of each arm in the study in the different islands. Hence, we aimed for a total sample size of 2,330.

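### The 90% power is not established for the randomised unit: the design effect is taken at the FCU, the PHCP correlation is dismissed partly on an invalid argument, and the planned Bonferroni adjustment is left out.

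*Protocol article*

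**What the plan says.** In the protocol article, Sample size calculation sizes each pairwise comparison as "needed to detect an absolute difference in Hba1c of 0.4" percentage points, "assuming a common standard deviation of 1.4% [40], a two-tailed power of 90%, and an alpha of 0.05". This gives 393 per arm. An FCU design effect (15 patients, intra-class correlation 0.01, interquartile range 0 to 0.032) raises it to 448 per arm, or 1,792 in total. A further 30% brings the target to 2,330.

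The same section acknowledges that PHCPs were the units allocated, but continues: "we considered that the intra-class correlation within PHCP was insignificant, and we used instead the intra-class correlation for FCU". It gives two reasons. The centres that make up a PHCP share only administration and some services. And: "Also, this effect was already controlled by means of the stratification".

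Random assignment states that "all FCUs at every PHCP were allocated to the same study group". It also describes four PHCPs per geographic stratum on the two large islands and four PHCPs on each small island, with arms equally represented.

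Statistical methods plans a multilevel model: "MLM adjusts for the clustering effects across three levels (patients, FCU, and PHCP) of the hierarchical data structure". For multiple comparisons the P "value will be adjusted with Bonferroni correction (Pc Z corrected value"). It names four contrasts: groups 1 and 2 each against usual care, then group 3 against groups 1 and 2.

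**The concern.** In a cluster-randomised trial, the precision of an arm contrast depends on the correlation within the unit that was randomised and on the number of those units. Here that unit is the PHCP, with 56 to 90 patients, and there are only 8 per arm. Even a small correlation at that level inflates the variance more than the same correlation within groups of 15.

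The stratification argument does not remove the problem. With one PHCP per arm in each stratum, stratification takes out differences between areas. A difference between two PHCPs in the same area cannot be separated from the difference between their arms.

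Statistical methods then uses both features that the sample size omits: a PHCP level and a multiplicity-adjusted alpha. Recruitment is complete, so what is at stake is interpretation. A non-significant contrast read against 90% power could be taken as stronger evidence of no effect than the design supports.

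**Working it through.** **Inputs.** Difference 0.4, SD 1.4, 90% power, alpha 0.05, 393 and 448 per arm, FCU size 15, FCU correlation 0.01 with upper quartile 0.032 (Sample size calculation); two-sided tests ("All tests will be two-sided with a type I error of 5" per cent), PHCP level and Bonferroni (Statistical methods); 12 + 12 + 4 + 4 = 32 PHCPs (Setting and recruitment), equally allocated, so 8 per arm; 90 patients intended per PHCP (Random assignment).

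**The plan's own figures.**
- Stated inputs: n = 2(1.960 + 1.282)² × 1.4²/0.4² = 257.4, so 258 per arm, not 393. Keeping two-sided 90% power, Bonferroni for 4, 5 or 6 comparisons gives 350, 365 or 377, so these do not give 393 either.
- From 393 the later steps do follow: 1 + 14 × 0.01 = 1.14; 393 × 1.14 = 448; 448 × 4 = 1,792; 1,792 × 1.3 = 2,330.
- With 448 per arm and design effect 1.14, SE = 1.4 × √(2 × 1.14/448) = 0.0999 and 0.4/0.0999 = 4.0. The normal approximation then gives 98% power at alpha 0.05, not 90%.

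**Patients per PHCP.** 448/8 = 56; 2,330/32 ≈ 73; intended 90.

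**Design effect at the randomised unit.** With ICC_FCU the correlation between patients of the same FCU and ICC_PHCP that between patients of different FCUs in the same PHCP:

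DE = 1 + (m_FCU − 1) × ICC_FCU + (FCUs − 1) × m_FCU × ICC_PHCP.

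Patients of one FCU also share its PHCP, so ICC_FCU should not be below ICC_PHCP. With 56 per PHCP and 15 per FCU, the last multiplier is 56 − 15 = 41.
- ICC_PHCP 0.005, ICC_FCU 0.01: 1 + 0.14 + 41 × 0.005 = 1.345
- Both 0.01: 1 + 0.14 + 0.41 = 1.55
- Both 0.032: 1 + 55 × 0.032 = 2.76

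**Power.** SE = 1.4 × √(2 × DE/448). Power comes from a non-central t with non-centrality 0.4/SE. The df are 28 (32 PHCPs − 4 arms), or 21 if eight strata are also fitted (31 − 3 − 7). Bonferroni over four contrasts gives alpha 0.05/4 = 0.0125.

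| ICC_PHCP (assumed) | DE | Effective n per arm | SE | Power, alpha 0.05 | Power, alpha 0.0125 |
|---|---|---|---|---|---|
| 0.005 | 1.345 | 333 | 0.1085 | 94% | 82–84% |
| 0.01 | 1.55 | 289 | 0.1165 | 91% | 75–77% |
| 0.032 | 2.76 | 162 | 0.1554 | 69–70% | 45–47% |

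Ranges run from 21 to 28 df. If group 3 against usual care is added from the Discussion, making five contrasts, the last column becomes about 79–81%, 72–74% and 42–44%.

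**Break-even.** At alpha 0.05, power stays at 90% up to a PHCP correlation of about 0.011. At alpha 0.0125 it is already 89–90% with a PHCP correlation of zero (DE 1.14).

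**More patients per PHCP.** At 90 per PHCP (720 per arm) and correlation 0.01, DE = 1 + 89 × 0.01 = 1.89 and effective n = 720/1.89 = 381. Power is 96–97% at alpha 0.05 and 87–89% at 0.0125. Effective n cannot exceed 8/ICC_PHCP. That is 800 at 0.01, but 8/0.032 = 250 at 0.032, below the 258 needed.

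**The case against.** The choice is disclosed and argued, and the planned model includes the PHCP level, so the inference itself does account for clustering at the randomised unit. That stands: this is a point about the power claim, not about the validity of the analysis.

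A reader might infer that the trial does not have 90% power. The documents do not support that flat statement. They give no PHCP correlation. At the plan's central value of 0.01, which is also the most the PHCP correlation can be if the FCU value is 0.01, power is 91% at the stated alpha of 0.05. The value 0.032 is the upper quartile of a correlation quoted for FCUs, and using it for PHCPs means raising the FCU value too.

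The number of comparisons in the Bonferroni family is not stated as a figure. Four is a count of the contrasts named, and an unseen analysis plan may fix another number.

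A reader might also infer that more patients per PHCP could not help. They do help at 0.01; a ceiling below 258 arises only near 0.032.

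Finally, the argument about loosely linked centres is a reasonable ground for expecting a small PHCP correlation. It is not the same as zero, and no estimate accompanies it.

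**Conclusion.** The concern holds in this form: 90% power is not established for the planned analysis at the randomised unit. Two parts need no assumption. The stratification argument is wrong given one PHCP per arm per stratum, and the sample size leaves out the PHCP level and the Bonferroni adjustment that Statistical methods specifies.

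The size of the effect does rest on assumptions: PHCP correlation 0.005 to 0.032, FCU correlation 0.01 or equal to the PHCP value if that is higher, 448 analysed per arm, and four contrasts. On these, power runs from about 94% down to 69–70% at alpha 0.05, and from 82–84% down to 45–47% after Bonferroni. Where 90% is kept at a PHCP correlation of 0.01, it is kept by the unexplained excess of 393 over 258, not by the reasoning given.

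**What to change.** In Sample size calculation:

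1. Delete the sentence claiming that stratification controls the PHCP effect. If the argument about separate centres is kept, support it with a PHCP correlation or label it an assumption.
2. State the design effect at the PHCP with the three-level formula above, ICC_FCU not below ICC_PHCP, 8 PHCPs per arm and t-based degrees of freedom.
3. Replace the single 90% with power, or detectable difference, over a range of PHCP correlations (for example 0.005, 0.01 and 0.032), at both 0.05 and the planned Bonferroni alpha, naming the contrasts counted.
4. Correct 393, or state the inputs that produce it, since those printed give 258.

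This changes text only; it needs no extra enrolment and no change to the analysis model. The cost is that the stated power becomes less favourable.

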#### Cost-effectiveness analysis

We will undertake a detailed analysis of the cost and the cost-effectiveness of each of the four groups in comparison to the others. Our analysis will conform to accepted economic evaluation methods. We will estimate cost and cost-effectiveness for the ‘within-trial’ period (2 years/short-run model) and also over the expected lifetime of the patient (lifetime/long-run model).

##### Short-run model

The cost-effectiveness measures in the two-year model will be the incremental cost per quality-adjusted life year (QALY) gained. QALYs will be calculated based on the HRQoL data collected during the trial. HRQoL will be measured according to the EQ-5D-5 L, which will be collected at baseline and at each follow-up visit for each individual patient. Patient-specific utility profiles will be constructed assuming a straight line relation between each of the patients’ EQ-5D-5 L scores at each follow-up point. The QALYs experienced by each patient from baseline to 2 years will be calculated as the area underneath this profile. We will investigate differences in baseline characteristics and, if necessary, use regression methods to control for them. As explained above, costs included in the analysis are those incurred by the healthcare service. Cost-effectiveness will be calculated as the incremental cost-effectiveness ratio (ICER) by dividing the estimated differences in costs by the differences in effects observed. Nonparametric methods to calculate confidence intervals around the ICER based on bootstrapped estimates of the mean cost and effect differences will be used. The bootstrap replications will also be used to construct a cost-effectiveness acceptability curve, which will reveal the probability that each alternative is cost-effective at 2 years for different values of willingness to pay for an additional unit of effectiveness. We will also subject the results to extensive deterministic (one-, two-, and multiway) sensitivity analysis.

##### Long-run model

The interventions under evaluation in this study are likely to have an impact beyond the trial period. To capture these potential effects, we will extrapolate the results to an extended time horizon in the analysis, i.e., considering the remaining life expectancy of the patients.

We will consider the potential application of the Centers for Disease Control-Research Triangle Institute (CDC-RTI) Diabetes Cost-Effectiveness Model [50] to estimate long-term outcomes in our population. The CDC-RTI Diabetes Cost-Effectiveness Model is a validated simulation model of disease progression and cost-effectiveness for T2DM based on data from the UK Prospective Diabetes Study (UKPDS) [51] and other sources. The aim of this model is to simulate the development of T2DM-related complications on three microvascular disease paths (nephropathy, neuropathy, and retinopathy) and two macrovascular disease paths (coronary heart disease and stroke). The model structure is based on a Markov model which simulates the progression of a patient based on estimated transition probabilities between possible disease states. In the CDC-RTI Diabetes Cost-Effectiveness Model, transition probabilities depend on risk factors—including HbA1c and cholesterol concentrations.

Following decisions about model structure to estimate future outcomes, a list of parameter estimates required for the model will be developed. Data from the trial will be used to input the model in order to estimate the long-term cost-effectiveness of the different alternatives, alongside relevant data from the published literature. The specific details of the data to be used to populate the model will be determined following the development of the structure and the systematic literature searches to identify available evidence. The cost-effectiveness measure will again be expressed in terms of the ICER for each alternative after discarding dominated strategies. We will undertake deterministic (one-, two-, and multiway) and probabilistic sensitivity analysis, the latter assuming appropriate distributions and parameter values [52].

#### Duration of fieldwork

Fieldwork is estimated to last 3 years. The first year to complete recruitment of patients and healthcare providers in primary care and the following 2 years for follow-up and measurement. As interventions are maintained over time, the period of intervention and follow-up overlap (Figure 1).

#### Monitoring

Trial monitoring is the responsibility of a research team in charge of all quality control activities, assessing adherence to the trial protocol: timely work plan execution and comprehensiveness of data acquisition and data quality (databases have been designed to avoid downloading inappropriate values for every variable). The interactive group sessions for patients and family members, as well as those for primary care physicians and nurses, are being recorded to monitor the quality of the intervention and its adherence to the predefined script.

### Trial status

Recruitment is complete and the trial is ongoing.

## Discussion

The ongoing INDICA study is a four-arm RCT involving all main actors playing a role in decision-making in T2DM (patients, families, physician and nurses). The INDICA study will assess the comparative effectiveness and cost-effectiveness of usual care for T2DM patients against three multicomponent education and coaching interventions. These interventions combine conventional group educational and training activities with different ICT-based interventions to guide the decisions of T2DM patients, families, and primary care healthcare professionals, according to evidence-based guidelines. The primary analysis is aimed at comparing the mean 24-month HbA1c (operationalized as HbA1c % change from baseline) among patients with T2DM whose PHCPs were assigned to the usual care group with the mean 24-month HbA1c % change among patients with T2DM whose PHCPs were assigned to the three different intervention groups. The study used cluster randomization to reduce the risk of contamination bias, since the educational parts of the multicomponent interventions for patients and healthcare professionals were applied to groups.

The importance of glucose control in T2DM has been confirmed in a meta-analysis [53]. The high incidence of macrovascular complications, such as myocardial infarction, stroke, and lower-limb amputations, are a major cause of disability, mortality, and economic losses. Microvascular complications, including retinopathy, neuropathy, and kidney disease also account for a highly significant morbidity, mortality, and economic burden [54] among patients with T2DM. The incidence of these complications and their healthcare and social and economic consequences is higher in the Canary Islands than in the rest of Spain and most western countries [2-4].

The interventions assessed by the INDICA study are based on the conceptual framework of behavioral change and patient-centered care [29,34]. There is increasing evidence that good self-care is related to improved T2DM outcomes [10,11,55,56]. Provider education and continuous feedback to patients and the use of reminders have been associated with improvements in provider adherence to guidelines and with clinically significant improvements in patient outcomes [10,11,55,56]. Although ICT-based studies to improve diabetes self-management have grown rapidly, there is a substantial discrepancy between the demand for this healthcare delivery mode and the scientific evidence supporting its efficacy and cost-effectiveness. Most published studies are focused on single interventions exclusively aimed at patients and are limited by methodologic deficiencies related to small-sample sizes and inconsistent selection of outcomes and measurement instruments, as well as short follow-up periods [57]. Although several studies assessing the effectiveness of ICT-based interventions on diabetes outcomes have reported small but significant effect-sizes [18-22,58], very few have assessed cost-effectiveness. Cost-effectiveness is especially relevant for the assessment of ICT-based interventions aimed at prevalent chronic diseases, given that the highest costs of the interventions correspond to the development of ICT applications whose effectiveness will become blurred over time as well as with their use by thousands of patients and physicians. In the current times of financial crisis, interventions not only have to prove effectiveness but also cost-effectiveness to reduce uncertainty in healthcare policy decision-making to contribute to the economic sustainability of public healthcare services. Consequently, while much is promised by electronic communications and tele-health interventions, there is a lack of robust information to support decisions at patient, clinician, and healthcare policy decision-maker level.

The current worldwide availability of mobile phones and internet use across socio-economic, gender, and age groups, combined with their unique ability to process and communicate data in real-time, make them an ideal platform to create simple, effective, and real-time diabetes management programs that can be used for large groups of patients. Few previous studies of electronic communication interventions for T2DM are randomized, include a control group, or involve more than one treatment group to evaluate complex or multicomponent interventions for all actors involved, not only from the effectiveness perspective but also the assessment of cost-effectiveness. This approach will improve transferability by extending the usefulness of the expected results beyond patients and clinicians in primary care to healthcare policy decision-makers.

## Abbreviations

BMI: Body mass index
CIHS: Canary Islands Health Service
CPG: Clinical practice guidelines
CT: Clinical test
DM: Diabetes mellitus
DST: Decision support tool
eGFR: Estimated glomerular filtration rate
ECR: Electronic clinical records
F to F: Face-to-face interview
FCU: Family Care Unit
HbA1c: Glycated hemoglobin
HRQoL: Health-related quality of life
ICER: Incremental cost-effectiveness ratio
ICT: Information and communication technology
M: Month
OCT: Optical coherence tomography
PHCP: Primary healthcare practices
QALY: Quality-adjusted life year
RCT: Randomized controlled trial
SMS: Short message service
SRI: Self-reported interview
T2DM: Type 2 diabetes mellitus
